#### Cost data

The research team will carry out a cost-effectiveness analysis of the intervention. Costs will be assessed from the hospital's perspective. The time horizon for costs and outcomes will be the patient's ICU stay. We will measure costs using a calculator under development, based on the cost data collected in the sub-study of costs within the IMPACTO MR platform.^(21)^ The collected data on costs consist of ICU staff, depreciation, electricity, water, telephone, internet, medical gases, overhead, office supplies, drugs, medical supplies, hemodialysis, blood transfusions, laboratory tests, and imaging tests. The researchers will adjust the costs by the Extended National Consumer Price Index (IPCA -*Índice Nacional de Preços ao Consumidor Amplo*) of the *Instituto Brasileiro de Geografia e Estatística* (IBGE) at the time of the cost analysis.^(22)^

#### Data collection and management

Trained healthcare workers collect data in each participating center using the Epimed system. The local infection control committee provides data on HAIs, and the data collectors enter it into a developed Research Electronic Data Capture system (REDCap, USA) via the internet, hosted on a server at *Hospital Israelita Albert Einstein* in São Paulo, Brazil. Access to all documents is controlled by user and password. To ensure data quality, we perform the following procedures: all professionals responsible for data collection are trained before the beginning of the trial; a researcher assistant from the coordinating center is responsible for solving any questions about data collection; a researcher from the coordinating center monitors the records of bed disinfection carried out by the hygiene team with the ICU discharges generated in the Epimed system weekly; the coordinating center assigns a researcher assistant to monitor the study participating centers; all the information obtained during the monitoring visits is confidential.

### Data monitoring

#### Interim analysis

Since the study's intervention is conducted in the environment and not directly on patients, we do not anticipate substantial risks to the study's performance. Therefore, we did not plan interim analyses. Adverse events are not expected to occur, but local researchers, data assistants, and local clinicians may report them. In any case, the research team assesses adherence to the intervention monthly by monitoring the exact number of bed disinfections after discharge, the volume of organosilane used (in mL), and the number of HAIs reported.

#### Auditing

Trial conduct is subjected to audit by Einstein Research Integrity Committee, at any time, independently of the institutional review board (IRB) and research team.

#### Sample size

We based the sample size calculation on a baseline incidence of HAIs of 9.88%, as indicated by preliminary data from a sample of the IMPACT MR platform cohort study conducted from 2018 to 2020.^(23)^ Assuming 556 patients per unit over 6 months, with a within-cluster within-period correlation of 0.01, a within-cluster between-period correlation of 0.008, a significance level of 5%, and a power of 80%,^(24)^ the study required a total of 14 participating units to detect a relative reduction of 20.2% (equivalent to an absolute reduction of 2%) in HAI rates due to the intervention. The estimated total number of patients across all participating units is 15,558.

After establishing the initial 14 centers, consideration was given to include two additional centers, bringing the total to 16. If we included these additional centers in the sample size calculation while maintaining all other parameters constant, it would require 411 patients per cluster per period, resulting in a total of 13,138 patients. However, the two additional centers ultimately did not participate in the study.

### Statistical analysis plan

We will present baseline data as the mean ± standard deviation (SD) for continuous variables with a normal distribution, or as the median [first quartile – third quartile] for non-normal distributions, and categorical variables as counts and percentages. We will report effect estimates for primary and secondary outcomes with 95% confidence intervals. All statistical tests will be two-sided, with a 5% significance level.

We will conduct all statistical analyses using R software version 4.2.2 or higher (R Core Team, 2022). We will not perform imputation for missing data on outcomes; all outcomes will be analyzed using complete case analysis.

The primary outcome analysis will estimate the risk ratio (RR) of HAIs between the intervention and control arms using a mixed logistic regression model. This model will incorporate random effects for clusters and cluster-period effects while adjusting for SAPS 3 and ICU size. If more than 5% of the SAPS 3 data are missing, we will apply multiple imputations under the assumption that the data are missing at random (MAR). We will proceed to the imputation using multivariate imputation by chained equations (MICE) based on patient characteristics (age, type of admission, and SOFA scores) using the ‘mice’ R package.^(25)^

As a sensitivity analysis for the primary outcome, we will use a complete-case analysis with the same mixed logistic regression model.

We will conduct a subgroup analysis of the primary outcome based on the type of admission, categorized as medical, elective surgical, and unplanned surgical.

We will analyze secondary outcomes using the same mixed logistic regression model used for the primary outcome.

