### Study setting

We propose a cluster study with a crossover in ICUs participating in the IMPACTO MR platform.^(16)^ The research team initially selected 16 ICUs, but two ICUs withdrew from the trial after randomization and before initial patient recruitment.

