### Intervention and usual care

The professionals from the hygiene and cleaning teams of the participating centers and their leaders received remote online training, which was replicated several times by the coordinating center with the support of a specialist nurse from the study.

During the 6 months of the study intervention, the hygiene/cleaning team at the participating centers proceeds with the terminal cleaning of the vacant bed using detergent and then applies the organosilane to it, aerosolizing the room from the back to the door and from top to bottom. After this process, the person responsible for the application moistens the cloth with organosilane and then rubs it on highly touched surfaces, such as furniture (e.g., the bed, chair, bedside table, gauze panel, communication panel, IV stand, dining table, and other furniture). The hygiene team uses organosilane both in single-bed and multi-bed ICUs whenever there is a need for terminal cleaning of the bed when the patient is discharged. During the intervention period, the hygiene team completed a form for each terminal cleaning performed using organosilane. This form assessed the length of time the patient spent in the ICU, whether they were under precautions or isolation, the time of day, and the total time of completion of the process.

During the 6 months of usual care, the hygiene/cleaning team disinfects the beds and environment according to their established protocols, using standard products.

After a 1-month washout period, the units previously randomized to organosilane crossover back to their usual disinfection regimen, while the units randomized to usual disinfection will receive the organosilane intervention (Figure 1).

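### The primary crossover model lists no fixed period effect, so a common change in HAI risk between the two periods would cost power and, if the sequences are unequal, would also bias the estimate

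*Protocol article*

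**What the plan says.** The Statistical analysis plan section estimates the treatment effect "using a mixed logistic regression model" and describes its terms: "This model will incorporate random effects for clusters and cluster-period effects while adjusting for SAPS 3 and ICU size". The same model is used for the complete-case sensitivity analysis and for the secondary outcomes. Neither that section nor any other part of the article names period as a fixed effect.

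The design is a two-period crossover. Under Intervention and usual care: "After a 1-month washout period, the units previously randomized to organosilane crossover back to their usual disinfection regimen", while the other units move to organosilane. The Abstract gives the window as November 2023 to December 2024, and Trial status gives a start on 6 November 2023. The first period therefore runs to about early May and the second from about early June to early December.

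Randomization was 1:1, stratified by ICU size. Under Study setting, "two ICUs withdrew from the trial after randomization and before initial patient recruitment", which leaves 14 of 16. The sequences to which those two had been assigned are not given.

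**The concern.** In a two-period crossover each ICU's treatment contrast is also a contrast between periods. If infection risk changes between periods in all ICUs alike, that change enters the contrast with one sign in ICUs that start on organosilane and the opposite sign in the others. A fixed period effect removes it.

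The random ICU-period effect does not. It has mean zero and is independent across ICUs, so a shared shift can only be absorbed as extra variance. Nor can the ICU-period effects be read as fixed: treatment is constant within each ICU-period, so its effect could not then be identified. SAPS 3 adjusts for severity at admission, not for season or for changes in practice or surveillance.

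At stake is power in a design with little to spare and, if the two sequences are unequal, the estimate itself.

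**Working it through.** **Inputs from the Sample size section.** "baseline incidence of HAIs of 9.88"%; the aim to "detect a relative reduction of 20.2% (equivalent to an absolute reduction of 2%) in HAI rates", hence 9.88% against 7.88%; 556 patients per ICU per period; 14 ICUs; correlations 0.01 within period and 0.008 between periods; "a significance level of 5%, and a power of 80"%. Tests are two-sided. **Assumed, because the article gives neither:** the size of any period shift, and the sequence split.

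**1. The plan's own figure.**
- Patients per arm without clustering: (1.960 + 0.842)² × (0.0988×0.9012 + 0.0788×0.9212) / 0.02² = 3,172.
- Design effect: 1 + 555×0.01 − 556×0.008 = 2.102.
- ICUs: 3,172 × 2.102 / 556 = 12.0, or 14 after the usual addition of one per sequence.
- Power with 14 ICUs: 0.799 on 13 df and 0.793 on 12 df.
- Total: 14 × 2 × 556 = 15,568, against 15,558 stated, a rounding difference.

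The plan's figure reproduces, and it leaves almost no slack.

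**2. Variance of one ICU's treatment contrast, log-odds scale.**
- Target effect: logit(0.0788) − logit(0.0988) = −0.248.
- ICU-period variance: (0.01 − 0.008) / (0.0988×0.9012) = 0.0225.
- Sampling variance: 1/(556×0.0890) + 1/(556×0.0726) = 0.0450.
- Total: 2×0.0225 + 0.0450 = 0.090.

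**3. Effect of leaving out period.** Let d be the period log odds ratio (period 2 against period 1) and θ the treatment effect. The contrast centres on θ − d in ICUs that start on organosilane and on θ + d in the others. With 7:7 the mean is still θ, but the observed variance of the contrasts rises by about d².
- 1-point fall (9.88% to 8.88%): d = −0.118, d² = 0.014, variance 0.104.
- 2-point fall (9.88% to 7.88%): d = −0.248, d² = 0.062, variance 0.152.

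Closed-form power on 12 df is 81% with no shift, 75% at 1 point and 59% at 2 points.

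**4. Simulation at 7:7.** This analyses within-ICU contrasts, as a stand-in for the mixed logistic fit.

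| Assumed shift | Power without period | Power with period |
|---|---|---|
| None | 0.81 | 0.80 |
| 1-point fall | 0.75 | 0.79 |
| 2-point fall | 0.58 | 0.78 |

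At a 2-point fall the type I error without the term is about 1.3%, so the test is conservative. A separate run with a 20% relative rise gave 0.66 without the term and 0.80 with it. Fits of the mixed logistic model itself showed the same pattern at a higher level (about 84% with the term; 78% and 64% without it at 1 and 2 points). The conclusion rests on the table, which agrees with the closed form and with the plan's own 80%.

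**5. Unequal sequences.** With n₁ ICUs starting on organosilane and n₂ starting on usual care, the estimate without a period term centres on θ + d(n₂ − n₁)/14. The bias at 8:6 or 6:8 is one seventh of d in size.
- 8:6, 2-point fall: −0.248 + 0.248/7 = −0.213, an attenuation of 14%. Simulated power is 43% without the term and 77% with it.
- 6:8, same fall: −0.248 − 0.248/7 = −0.284, an exaggeration of 14%.
- On the risk scale, a 10% relative shift biases the estimate by 0.14 points, or 7% of the 2-point target.

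**The case against.** **The article is a condensed account.** The full protocol or analysis plan may contain a period term, and the quoted sentence does not even name the treatment term. That tempers certainty about what will be run. But the sentence does set out the random effects and the adjustment covariates, and an analyst who follows it would fit no period effect.

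**The loss is conditional.** The documents give no seasonal or secular infection data. With no shift the omission costs nothing, and a 2-point shift is as large as the whole target effect. At a 10% relative shift, a normal approximation gives 0.857 falling to 0.817, still above 80%. This stands: power cannot be said to fall below 80% without an assumed shift. Nor does the period term guarantee 80%, since t-based power with it is about 76–80% across the no-shift and falling-risk cases examined at 7:7.

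**Stronger readings that the documents do not support.** A reader might infer that the crossover's main advantage is lost. It is not: the main gain is the removal of between-ICU variation, which the random ICU effect keeps and on which the sample size relies through the 0.008 correlation. A reader might also infer that the result will be biased or falsely positive. At 7:7 with ICUs of equal size there is no bias and the error is on the conservative side. At 8:6 with a 2-point shift the false-positive rate is still only about 2.4%. No passage states an 8:6 split, and 7:7 fits the text equally well.

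**Conclusion.** The point holds as an avoidable and conditional loss of efficiency, with a conditional risk of bias. As described, the primary model cannot remove a shift common to all ICUs. Under the plan's inputs the cost is about 4 points of power for a 1-point fall (0.75 against 0.79) and about 20 points for a 2-point fall (0.58 against 0.78). Including the term costs about 1 point or less at 7:7 when there is no shift.

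Bias needs both a shift and an imbalance between sequences. At 8:6 or 6:8 it is one seventh of the period log odds ratio, about 14% of the target effect for a 2-point shift, and can run in either direction. Unequal ICU volumes could create some imbalance even at 7:7.

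The shift sizes and the unequal splits are assumptions. The missing term, the two calendar periods and the unstated split come from the article. The case for acting is the asymmetry between a small fixed cost and a possibly large loss.

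**What to change.** Add period (1 versus 2) as a fixed effect in the primary model, its sensitivity and subgroup analyses, and the models for the binary secondary outcomes. Keep both random effects, SAPS 3 and ICU size. If the full analysis plan already includes the term, say so in the description of the model. ICU cost is not binary and needs its own model, which is a separate matter.

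Report how many of the 14 ICUs are in each sequence, and to which sequence the two withdrawn ICUs had been assigned.

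The change is one line of text and one degree of freedom, with no new data. It should be recorded before the blinded statistician learns the allocation, because a period term added afterwards would be open to challenge.

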### Outcomes

The primary outcome is the incidence of HAIs (i.e., VAP, CLABSI, and CA-UTI) during the 6-month study period, as diagnosed according to the criteria of the *Agência Nacional de Vigilância Sanitária* (ANVISA)^(17)^ (Table 2). The secondary endpoints are the contamination of the environment by multidrug-resistant microorganisms (i.e. oxacillin-resistant *Staphylococcus aureus,* vancomycin-resistant Enter*ococcus faecium,* carbapenem-resistant Enterobacter, *Pseudomonas* and *Acinetobacter*) at the end of each phase of the study; the incidence of each specific monitored HAI (VAP, CLABSI, and CA-UTI) and the cost of the patient's ICU stay.

**Table 2 t2:** *Agência Nacional de Vigilância Sanitária* diagnostic criteria for healthcare-related infections

Healthcare-associated infection	ANVISA diagnostic criteria
Ventilator-associated pneumonia	Patient with two or more consecutive days of invasive mechanical ventilation use with no underlying heart or lung disease ***AND*** One of the following findings on thorax imaging tests, whether new, persistent, or progressive: − Infiltrate − Opacification/consolidation − Cavitation − Pneumatocele ***AND*** At least one of the signs and symptoms: − Fever (temperature: > 38ºC), with no other associated cause − Leucopenia (< 4,000 cells/mm3) or leucocytosis (> 12,000 cells/mm3) − Altered level of consciousness, with no other apparent cause, in patients ≥ 70 years ***AND*** At least two of the signs and symptoms: − Appearance of a purulent secretion or a change in the characteristics of the secretion or increased respiratory secretion or increased need for aspiration − Apnea, tachypnea, dyspnea, or cough (new or worsening episode) − Auscultation with wheezing, snoring, or rales (new or worsening episode) − Worsening of gas exchange, desaturation, increased oxygen demand, or increased ventilatory parameters for at least 2 days
Central line-associated bloodstream infections	− Patient using a central catheter for more than two consecutive days ***AND*** − Presents a pathogenic bacterial or fungal microorganism identified from one or more blood samples obtained in a hemoculture ***OR*** − Identified genus and species, or at least genus, by validated non-culture-based test methods ***AND*** − The identified microorganism is not related to another infectious focus

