Catheter-associated urinary tract infection	− Patient using an indwelling bladder catheter for more than two consecutive days ***AND*** − Has at least one of the following signs and symptoms, with no other recognized causes: − Fever (T > 38ºC) − Suprapubic pain or discomfort − Lumbar pain or discomfort − Hematuria − Urinary urgency − Increased urinary frequency − Dysuria ***AND*** − Positive urine culture with a maximum of two bacterial species with a colony count ≥ 10^5^ CFU/mL

ANVISA - *Agência Nacional de Vigilância Sanitária*; T - temperature.

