### Data collection

#### Clinical data

We will extract patient data from the Epimed system,^(18)^ which provides data in a manner that makes it impossible to identify patients. The data collected consists of sex and age, ICU admission data (date of admission to the ICU and hospital, comorbidities, severity measured by the Simplified Acute Physiology Score 3 (SAPS 3) and Sequential Organ Failure Assessment (SOFA) scores, type of ICU admission (clinical, elective surgical, or unplanned surgical), reason for admission, use of a central venous catheter, mechanical ventilation, and indwelling bladder catheter; development of HAIs, microbiological cultures, vital status and date of ICU and hospital discharge.

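### Adding type of admission, and device status on the day of ICU admission if it can be extracted, to the primary model would buy some precision cheaply

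*Protocol article*

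**What the plan says.** The Statistical analysis plan section closes the covariate set of the primary model: "This model will incorporate random effects for clusters and cluster-period effects while adjusting for SAPS 3 and ICU size". The same model is carried over to the secondary outcomes. Type of admission appears twice in that section, as a predictor in the imputation of SAPS 3 and as the subgroup variable, but not as a covariate.

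The Clinical data section lists type of ICU admission among the data collected, and then "use of a central venous catheter, mechanical ventilation, and indwelling bladder catheter; development of HAIs". The list opens a bracket after the ICU admission data and never closes it, so the time point at which device use is recorded is not explicit.

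Table 2 in the Outcomes section ties each component of the primary outcome to a device. For pneumonia it asks for "Patient with two or more consecutive days of invasive mechanical ventilation use", and for urinary infection "Patient using an indwelling bladder catheter for more than two consecutive days". The bloodstream criterion is the analogous one for a central catheter.

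**The concern.** Each ICU is its own control, so the treatment effect is estimated mainly from the difference between an ICU's two periods. A covariate improves that contrast only if it varies between patients or between periods within an ICU. ICU size hardly does, and whatever it explains between ICUs is already taken up by the random cluster effect. That leaves SAPS 3, a general severity score.

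If an ICU's mix of elective-surgical, ventilated or catheterised patients differs between its two periods, whatever SAPS 3 does not capture ends up in the cluster-period variance. It widens the confidence interval and, with 14 ICUs, can leave a chance case-mix imbalance between arms. Characteristics fixed at ICU admission precede any event in Table 2, so adjusting for them can recover part of that precision. At stake is a narrower interval, for the primary outcome and for the three infection-specific outcomes analysed with the same model.

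**Working it through.** **Inputs from the Sample size section.** Control risk ("We based the sample size calculation on a baseline incidence of HAIs of 9.88" per cent), the effect ("to detect a relative reduction of 20.2% (equivalent to an absolute reduction of 2%) in HAI rates due to the intervention", so 9.88% against 7.88%), cluster-period size ("Assuming 556 patients per unit over 6 months"), correlations ("with a within-cluster within-period correlation of 0.01", and 0.008 between periods), 14 ICUs, two-sided 5%.

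**The plan's own figure.**
- Design effect = 1 + 555 × 0.01 − 556 × 0.008 = 2.102.
- Variance of the risk difference = (0.0988 × 0.9012 + 0.0788 × 0.9212) × 2.102 / (14 × 556) = 0.0000436; standard error 0.00661; noncentrality 0.02 / 0.00661 = 3.03.
- Power from the noncentral t distribution with 13 df = 79.9%. The stated 80% reproduces, and no covariate enters it.

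**Where the error sits.** The design effect splits into a patient-level part, 1 − 0.01 = 0.99, and a cluster-period part, 556 × (0.010 − 0.008) = 1.112. The second is 1.112 / 2.102 = 53% of the total, and period-to-period case-mix drift falls there.

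**Formula for the gain.** With adjustment, design effect = 0.99 × (1 − R²) + 1.112 × (1 − S). R² is the patient-level variance explained and S the share of cluster-period variance explained. For a binary predictor with prevalence q, risk difference RD and per-period drift SD s:
- R² = q(1 − q)RD² / 0.0890
- S = s²RD² / (0.002 × 0.0890)

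Here 0.0890 = 0.0988 × 0.9012. The values of q, RD and s are assumptions, since the documents give none of them.

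| R² | S | Design effect | Power (13 df) |
|---|---|---|---|
| 0 | 0 | 2.102 | 79.9% |
| 0.03 | 0 | 2.072 | 80.5% |
| 0.11 | 0 | 1.993 | 81.9% |
| 0.03 | 0.20 | 1.850 | 84.6% |
| 0.11 | 0.20 | 1.771 | 86.1% |

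Worked case: 35% ventilated at admission, risk ratio 4.5, s = 4 points. Unventilated risk = 0.0988 / (0.65 + 0.35 × 4.5) = 0.0444; RD = 3.5 × 0.0444 = 0.155; R² = 0.062; S = 0.217; design effect 1.800; power 85.6%. If 4 points is instead read as the SD of the difference between two periods, S halves and power is 83.3%.

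The formula ignores SAPS 3, which may already absorb part of this, so simulation is the better guide.

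**Simulations with SAPS 3 or a severity score already in both models** (14 ICUs × 2 × 556, cluster-period analysis with 12 df).
- Adding ventilation at admission, 400 trials per setting: 80.5% to 81.8% (drift SD 2 points), 79.8% to 83.8% (SD 4), 80.3% to 86.5% (SD 6). The standard error falls by 2%, 5% and 8%.
- Adding a generic device indicator, 800 trials per setting: 81.4% to 82.2% with no drift, which is within simulation error. With drift of about 4 to 5 points and 50% prevalence: 84.5% to 86.1% (odds ratio 3), 84.9% to 89.4% (odds ratio 6), 87.5% to 92.1% (odds ratio 10). With 30% prevalence and odds ratio 6: 84.2% to 92.4%. Starting levels differ between settings, so only the differences should be read.

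The Monte Carlo error of a single power near 80% is √(0.8 × 0.2 / 400) = 2.0 points with 400 trials and 1.4 points with 800. Type of admission was not simulated separately, so its own contribution is not quantified.

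**Room for extra terms.** Expected events lie between 15,558 × 0.0788 = 1,226 and 15,558 × 0.0988 = 1,537, so a handful of baseline terms is no burden.

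**The case against.** The strongest reply is that nothing in the plan is wrong. Adjusting for the stratification factor and one severity score is a defensible, prespecified choice. The 80% does not depend on covariates, and the random cluster-period effect carries case-mix drift into the standard error, so inference stays valid. All of that stands. A reader might infer that planned power is lost or that the result would be biased; the documents support neither.

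A reader might also infer that Table 2 makes a device at admission a precondition for every event. It does not. It requires about two or more days of a device during the stay, and a patient admitted without one can receive it later and have an event. Admission status is a plausible predictor of unknown strength.

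It is also not established that admission-day device status exists as a variable. In the Clinical data section the device items run straight into infections, cultures and vital status, which belong to the whole stay. This makes the device terms conditional. It does not touch type of admission, which is known at entry.

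Large gains can be produced from the formula: with 25% ventilated, risk ratios of 2.5 to 4.5 and drift SD of 2 to 6 points it gives 80.9% to 94.9%. The top end needs ventilation at admission alone to explain 69% of the cluster-period variance and takes no account of SAPS 3, so it should not be quoted as an expected gain. The simulations, in turn, use a cluster-period contrast and not the planned mixed logistic model.

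Finally, changing the primary model of an open-label trial that was already collecting data has a credibility cost. It is limited if the change is dated and justified while the analyst is still blinded, as the Blinding section provides, and the present model is also reported.

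**Conclusion.** The point holds as a cheap improvement to a valid analysis. Of the two chosen covariates one is nearly inert in a crossover, while a baseline variable the protocol itself uses elsewhere, type of admission, is left out, and device status at admission may be available too.

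The size is modest and assumed: about 1 point of power if case mix is stable between periods; roughly 1 to 6 points with SAPS 3 already in the model and a drift SD of 2 to 6 points; up to about 8 points if device effects are very strong. These figures rest on assumed device prevalence, strength of association and drift, and the gain shrinks to the extent that SAPS 3 already captures the same information.

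**What to change.** Before unblinding, amend the covariate sentence in the Statistical analysis plan section so that the primary model adjusts for:

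- SAPS 3, ICU size and type of admission (medical, elective surgical, unplanned surgical);
- mechanical ventilation, central venous catheter and bladder catheter in place on the day of ICU admission (yes/no each), provided the sponsor first confirms that admission-day status can be extracted. If it cannot, add type of admission alone.

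State that device use at any time during the stay and device days are not used as covariates: they are post-baseline, and device days can be prolonged by the infection itself. Extend the existing imputation rule, which now covers SAPS 3 only, to the added covariates. Keep the SAPS 3 and ICU size model as a named sensitivity analysis. In the Clinical data section, close the bracket and state when device use is recorded.

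The cost is a few more model terms, the extraction of admission-day status, and a documented change to the primary model of an open-label trial. For type of admission no new data collection is needed.

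### If SAPS 3 is imputed, the stated imputation model leaves out HAI, ICU and arm, which weakens the severity adjustment; adding them is a modest improvement at no cost

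*Protocol article*

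**What the plan says.** All of this is in the protocol article, section Statistical analysis plan.

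- Analysis model: a mixed logistic regression for HAI by arm. "This model will incorporate random effects for clusters and cluster-period effects while adjusting for SAPS 3 and ICU size".
- Trigger for imputation: "If more than 5% of the SAPS 3 data are missing, we will apply multiple imputations", assuming missing at random.
- Imputation predictors: "using multivariate imputation by chained equations (MICE) based on patient characteristics (age, type of admission, and SOFA scores").
- Missing outcomes: "We will not perform imputation for missing data on outcomes; all outcomes will be analyzed using complete case analysis".
- The one sensitivity analysis named for the primary outcome: "As a sensitivity analysis for the primary outcome, we will use a complete-case analysis with the same mixed logistic regression model".

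The section does not say what happens to patients without SAPS 3 when 5% or less is missing. The article gives no expected rate of missing SAPS 3.

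**The concern.** An imputation model for a covariate should contain at least the variables of the analysis model in which the imputed values will be used. Here HAI, ICU and arm are in the analysis model and absent from the imputation list.

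- **HAI.** Without it, an imputed SAPS 3 value carries no information on HAI beyond what age, admission type and SOFA carry. The imputed patients dilute the association between SAPS 3 and HAI, and a larger sample does not cure this.
- **ICU.** Without it, a missing value is imputed as if all units had the same case mix, although the ICU is the unit of randomization and a random effect in the model.
- **Arm.** Without it, any difference in severity that arises between arms is missing from the imputed values, so the model corrects for only part of it.

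What is at stake is the quality of the severity adjustment and, only if the arms differ in severity, a small shift in the treatment estimate. A second, minor matter is that the 5% switch can make the sensitivity analysis identical to the primary analysis.

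**Working it through.** **1. The plan's own figure, used as the layout of the check.** From the section Sample size: 14 ICUs, 2 periods, 556 patients per ICU-period, 9.88% against 7.88%, correlations 0.01 and 0.008. 14 × 2 × 556 = 15,568, against 15,558 stated. The design effect is 1 + 555 × 0.01 − 556 × 0.008 = 2.102. With a noncentral t distribution on 13 degrees of freedom the power is 79.9%, so the stated 80% reproduces. The point does not touch the sample size.

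**2. Assumptions not in the documents.** Age, admission type and SOFA together explain R² = 0.4 of SAPS 3. The SAPS 3 log odds ratio is b = 0.6 per SD. Missingness f is 6%, 20% or 40%, unrelated to other variables. ICU enters the analysis as fixed indicators, for speed.

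**3. Attenuation of the SAPS 3 coefficient.** As a rule of thumb, the lost share is f × (1 − R²), because the imputed patients keep only the explained part of the association. At R² = 0.4 this gives 0.06 × 0.6 = 3.6%, 0.20 × 0.6 = 12% and 0.40 × 0.6 = 24%. Losses can be larger when SAPS 3 also varies between ICUs and the imputation ignores it. Simulated coefficients with the listed predictors:

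| Missing | Coefficient (true 0.60) | Attenuation |
|---|---|---|
| 6% | 0.57 | 5% |
| 20% | 0.50 | 17% |
| 40% | 0.41 | 32% |

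Adding the omitted variables removes the attenuation.

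Other inputs give a range. With b = 0.8 and R² = 0.4 the coefficient falls to 0.76, 0.67 and 0.58 (0.67/0.80 is a 16% loss, 0.58/0.80 about 28%). With b = 0.5 the loss at 20% missing is 12%, 8% and 4% for R² of 0.4, 0.6 and 0.8. At 6% missing it is 3.6%, 2.3% and 1.4%.

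**4. Treatment log odds ratio, SAPS 3 balanced between arms.** The shift against full data is about 0.001 to 0.009. In the b = 0.8 runs it is +0.001, +0.004 and +0.005 at 6%, 20% and 40% missing.

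**5. Treatment log odds ratio, arms differing by d SD.** Imputed values show no difference between arms, so the observed difference shrinks to (1 − f)d and is multiplied by the attenuated coefficient b′. The uncorrected part is approximately d × [b − b′(1 − f)]. For d = 0.1:

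- 6%: 0.1 × (0.60 − 0.57 × 0.94) = 0.006
- 20%: 0.1 × (0.60 − 0.50 × 0.80) = 0.020
- 40%: 0.1 × (0.60 − 0.41 × 0.60) = 0.035

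The simulated shifts are about 0.01, 0.02 and 0.04. As a stress case, b = 0.8 and d = 0.2 gave +0.053 at 20% missing (odds ratio 0.831 against 0.788) and +0.096 at 40% (0.857 against 0.779). The fuller imputation model gave about zero in both. The sign follows the direction of the imbalance.

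For scale, the planned effect is ln[(0.0788/0.9212)/(0.0988/0.9012)] = ln 0.780 = −0.248. A shift of 0.02 is 8% of that, and 0.04 is 16%.

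**6. The 5% switch.** At 5% or less missing, nothing is imputed and a model containing SAPS 3 drops patients without it. That is the same model on the same patients as the stated sensitivity analysis, so the difference between the two is zero. At most 0.05 × 15,558 = 778 patients are affected (650 if the roughly 13,000 of Table 1 is used). Cutting 556 to 528 per ICU-period lowers power from 79.9% to 78.9%.

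**The case against.** The strongest reply is that SAPS 3 is only an adjustment covariate. The target is the difference between arms, and that estimate hardly moves when SAPS 3 is balanced. SAPS 3 measures severity at admission, and every ICU contributes to both arms, so stable differences between units cancel. Nothing in the article suggests a 0.2 SD imbalance or 20% to 40% missing. All of this stands, and it is why the point is modest. It does not justify the shorter list, because the adjustment is there for the case in which some imbalance remains.

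A second reply is that the article condenses a fuller plan and does not say that only these predictors are used. That carries less weight: the article chose to name a specific list, and the list omits the outcome.

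A reader might go further in three ways that the documents do not support.

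- One might infer that the treatment effect will be materially biased. That needs both substantial missingness and an imbalance between arms, and neither is documented.
- One might infer that the harm is greatest when SAPS 3 is missing in particular ICUs. Concentrating the missing values in four ICUs added nothing in the simulation.
- One might read the 5% switch as a serious flaw. The handling at 5% or less is implied and not stated, complete-case estimates at that level differed from full data by about 0.003 or less, and with nothing imputed there is no imputation to test. Requiring imputation at any level, or a model without SAPS 3, is a preference and not a correction.

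Period is also a weak omission, since the stated analysis model names no fixed period effect.

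**Conclusion.** The point holds as a modest improvement. The article fixes an imputation list that omits HAI, ICU and arm, although its own analysis model contains all three. The SAPS 3 coefficient is then attenuated by about 5%, 17% and 32% at 6%, 20% and 40% missing. The treatment log odds ratio changes by less than 0.01 under balance, and by about 0.01, 0.02 and 0.04 at those rates with a 0.1 SD difference between arms. These sizes rest on the assumed R², SAPS 3 effect, imbalance and random missingness. The attenuation is smaller if age, admission type and SOFA predict SAPS 3 better than assumed. If 5% or less is missing, no imputation takes place and only the minor note about the coinciding sensitivity analysis remains.

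**What to change.** When imputation is triggered, add HAI status, arm and ICU to age, type of admission and SOFA in the same mice call. ICU can enter through a cluster-aware method or as indicators. Indicators also carry ICU size, which is a property of the unit. Period is optional. Run the imputation in patients with HAI status observed, which keeps to the rule that outcomes are not imputed.

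For the minor note, add one sentence: if 5% or less of SAPS 3 is missing, the primary analysis is complete-case and the sensitivity analysis uses the fuller imputation; above 5%, the roles are as now stated.

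The cost is one or two sentences in the analysis plan and a larger predictor matrix. HAI and SOFA are already available, and ICU and arm are known by design. No new data are needed and the sample size is unchanged. The change should be made before the statistician sees outcome data by arm.
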